## Methods

### Summary of Overall Study Design

This study will be a 3-arm RCT, including 2 active intervention conditions and 1 active control condition. Study procedures were preregistered in ClinicalTrials.gov before enrollment of the first participant (NCT03858881; recruitment start date: March 2019). The Stony Brook University Institutional Review Board (IRB) has approved all study procedures described below. Participants will be randomly assigned to one of 3 conditions in equal numbers. We opted for equal allocation across groups (a relatively conservative approach) rather than weighted allocation to the active intervention groups, owing to the novelty of the VR intervention being evaluated and the resulting need for a rigorous, controlled test of its efficacy. After qualifying for participation based on a phone screen, adolescents (and 1 caregiver per adolescent) will visit the Department of Psychology at Stony Brook University for a 2-hour laboratory visit. Adolescents and parents will complete baseline questionnaires (see below for details). Adolescents will then be randomized to receive one of 3 interventions using a computer-based random number generator: the VR GM intervention (VR GMI), the online GM intervention (online GMI), or an online active control program designed to replicate ST and tested previously [13,14]. Immediately after intervention completion, adolescents will complete a postintervention questionnaire battery. Adolescents and parents will then be asked to complete online follow-up questionnaire batteries 3- and 9-month postintervention.

### Subjects, Projected Screen Failure Rate, and Power Analysis

We intend to recruit 159 adolescents aged 12 to 16 years (inclusive). G*Power 3.1 ( University of Duesseldorf) was used to calculate the sample size needed to achieve sufficient power, (1- β) to detect mean group differences (based on an omnibus *F* test) of small (.2), medium (.5), and large intervention effects (.8) on depression symptoms, measured continuously, with alpha=.05 and power at 0.80 for a 3-arm randomized trial. Sample sizes calculated were 969, 159, and 66 for effects of .2, .5, and .8, respectively, for an omnibus one-way analysis of variance (ANOVA). Power to detect a small effect size is ideal, but logistical constraints necessitate a more conservative sample size. The sample size of 159 (53 per SSI condition) reflects power to detect a medium (*d*=.5) between-group effect size.

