### Follow-Up Assessments

To enable evaluation of the interventions’ effects on depressive symptoms and secondary study outcomes over time, each adolescent and parent will be invited to complete Qualtrics-based questionnaire batteries, including the same questionnaires as those they completed at their initial laboratory session. Links to Qualtrics surveys will be sent to families at 3- and 9-month follow-up points. Surveys may be conducted via phone at the family’s request. Families who do not complete the follow-up questionnaires within 3 days of receipt will receive up to 3 reminder messages from the research team to encourage survey completion.

Notably, logistical constraints necessitated our limiting the number of follow-up assessments in this study to 2 per family (at 3- and 9-month postintervention), and analyses were planned accordingly (see below for a more thorough description). We elected a final follow-up assessment at the 9-month mark to maintain consistency with previous trials of GMI [13,14].

After the study is complete, an aggregate results summary will be emailed to families. Condition assignment will be revealed at this time, and all youths will receive access to both Web-based interventions. Youths who did not receive the VR program will be invited to complete the intervention at Stony Brook University.

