#### Children’s Depression Inventory-2

Adolescent depressive symptom severity will be assessed using the CDI-2 [31] child form (youth-report) and parent forms (parent-report). The CDI-2 is a reliable, valid measure of youth depression severity, normed for youth age and sex and yielding raw and *T* scores. Changes in youth-report CDI-2 scores from baseline to each of the follow-up assessments (3-month and 9-month) will serve as the primary index of intervention effects. Changes in parent-report CDI-2 scores from baseline to each of the follow-up assessments (3-month and 9-month) will serve as a secondary index of intervention effects. The CDI-2 will not be administered to youths or to parents immediately postintervention, as we do not expect depressive symptom change to occur within the span of 1 study session. Changes in scores on other assessments will serve as secondary outcomes.

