## Results

### Aim 1: Attempt to Replicate Past Research

We will use mixed-effects linear models to test the hypothesis that interventions teaching GM (either VR or Web-based) predict reductions in adolescent depressive symptom severity (primary study outcome), per both adolescent and parent reports, relative to Web-based ST. Our study design, including 3 assessment points is structured to allow for detection of linear intervention effects. We will run additional mixed-effects linear models to assess whether interventions teaching GM predict larger improvements in secondary study outcomes (perceived primary and secondary control, hopelessness, loneliness, attitudes toward psychotherapy, and parent psychopathology) versus Web-based ST. Intervention condition will be a binary predictor variable in these models, with the VR GMI and Web-based GMI groups collapsed into a single *GM* intervention group. Potential covariates will include family income, age, sex, and time (baseline, postintervention where applicable, and 3-month and 9-month follow-up); each possible covariate will be included in analyses if it shows a significant association with a model outcome at baseline or any follow-up point (such associations are unlikely to occur, given randomization procedures, but remain possible). Models will include a random intercept and slope, an autoregressive error structure, and use full information maximum likelihood (FIML) estimation to address missing data. We will create 2 orthogonal planned contrasts for testing intervention effects. One planned contrast will examine whether the 2 active GM conditions differ from the ST control condition, whereas the other planned contrast will examine whether the VR-based intervention outperforms the Web-based intervention. A significant (*P*<.05) interaction between the first contrast and time would indicate that interventions teaching GM predicted significantly different 9-month change in an outcome relative to the control ST condition. We will also replicate these analyses for the most central symptoms of adolescent depression identified in previous analyses (*sadness*, *self-hatred*, and *loneliness*) and use Holm-Bonferroni corrections for multiple comparisons.

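### The recruitment target of 159 equals the number of complete outcomes the power calculation needs, so the stated 0.80 power makes no allowance for loss over 9 months

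*Protocol article*

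**What the plan says.** In the protocol article, the section on subjects, screen failure and power sets the target: "We intend to recruit 159 adolescents aged 12 to 16 years (inclusive"). The calculation was run "with alpha=.05 and power at 0.80 for a 3-arm randomized trial", and its results are given as "Sample sizes calculated were 969, 159, and 66 for effects of .2, .5, and .8, respectively, for an omnibus one-way analysis of variance (ANOVA"). The section concludes: "The sample size of 159 (53 per SSI condition) reflects power to detect a medium (*d*=.5) between-group effect size". It says that logistics ruled out powering for a small effect. It states no retention rate and no allowance for loss. Allocation is equal across the three arms (Summary of Overall Study Design).

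The section on the CDI-2 defines the primary outcome: "Changes in youth-report CDI-2 scores from baseline to each of the follow-up assessments (3-month and 9-month) will serve as the primary index of intervention effects". The CDI-2 is not given immediately after the intervention. Follow-Up Assessments describes online survey links, with telephone completion on request, and adds: "Families who do not complete the follow-up questionnaires within 3 days of receipt will receive up to 3 reminder messages". Participant Incentives offers a US $10 gift card per family for each completed follow-up. Under Aim 1, the mixed models will "use full information maximum likelihood (FIML) estimation to address missing data".

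**The concern.** The total from the power calculation is the number of youths who must supply an outcome, and the article uses the same number as its recruitment target. Any shortfall at 3 or 9 months therefore comes directly off the number on which the printed power rests. The document foresees such a shortfall, because it plans reminders for late responders and an estimation method for missing data.

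A youth lost after the laboratory visit has only a baseline CDI-2 score and adds almost nothing to a test of differential change. FIML uses the observed scores efficiently and limits bias if data are missing at random, but it does not recreate unobserved 9-month scores.

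What is at stake is how a null result is read. If VR does not separate from the Web-based program, a reader who relies on the printed 0.80 would take that as stronger evidence against VR than the calculation supports.

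**Working it through.** **Inputs.** From the power section: three arms, alpha .05, power 0.80, d=.5, N=159 (53 per arm). Loss rates and within-person correlations are my assumptions, since the article gives neither.

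**1. Reproducing the stated sample size.** For a one-way ANOVA with k=3, power = P(F' > F crit), where F' is noncentral F with (2, N−3) degrees of freedom and noncentrality N·f², and f = d/2. The smallest N divisible by 3 with power of at least .80 is:
- f=.10: 969
- f=.25: 159
- f=.40: 66

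All three match the article. Reading .2, .5 and .8 directly as f would give 246, 42 and 21, so the basis is not in doubt.

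**2. Margin at f=.25.**

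| Youths with outcome | Noncentrality N × .0625 | Power |
|---|---|---|
| 159 | 9.94 | .805 |
| 158 | 9.88 | .802 |
| 157 | 9.81 | .799 |
| 156 | 9.75 | .797 |

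The calculation tolerates one loss; the second takes it below .80.

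**3. Power at assumed losses, same ANOVA.** The number with outcomes is 159 × (1 − loss).

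| Loss | Number with outcomes | Power |
|---|---|---|
| 5% | 151.05 | .783 |
| 10% | 143.1 | .758 |
| 20% | 127.2 | .70 |
| 30% | 111.3 | .640 |

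**4. How far baseline data could offset this.** In an ANCOVA-type approximation the effective f is .25/√(1 − r²), where r is the baseline–outcome correlation. At r=.5 this is .25/.866 = .289.

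| r | No loss | 10% | 20% | 30% |
|---|---|---|---|---|
| .3 | .843 | .799 | .747 | .684 |
| .5 | .908 | .874 | .829 | .772 |
| .6 | .947 | .922 | .887 | .838 |

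**5. The planned contrast-by-time tests.** I assume linear time at 0, 3 and 9 months, compound symmetry with correlation rho, and a difference of .5 SD at 9 months. With complete data the variance of the 9-month difference is 81 × (1 − rho)/42 × (1/n1 + 1/n2). Here 42 is the sum of squared deviations of 0, 3 and 9 from their mean of 4 (16 + 1 + 25). For VR v Web at rho=.5: 81 × .5/42 × 2/53 = .0364, so SE = .191, .5/.191 = 2.62, and power is about .75. With monotone dropout, the generalised least squares information is averaged over the dropout patterns. Each cell gives VR v Web / GM v ST.

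| rho | No loss | 10% lost by 3 months, 20% by 9 | 15% lost by 3 months, 30% by 9 |
|---|---|---|---|
| .4 | .67 / .79 | .59 / .72 | .55 / .67 |
| .5 | .75 / .86 | .67 / .79 | .62 / .75 |
| .6 | .83 / .92 | .76 / .87 | .71 / .83 |
| .7 | .92 / .97 | .87 / .94 | .83 / .92 |

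Only the fall along a row is due to loss. The level at which a row starts reflects the correlation and the use of an omnibus calculation for two-group contrasts, which is a separate matter: a two-group t test at d=.5 with 53 per arm has power of about .72 with no loss at all.

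**The case against.** The strongest reply is that the trial will not run a completers-only ANOVA on a single follow-up score. It plans mixed models on baseline, 3- and 9-month data, and the outcome is change. A reader might infer from the ANOVA figures that 0.80 power cannot be reached at any realistic retention. The document does not support that. At a baseline correlation of .5 the ANCOVA-type approximation still gives about .83 at 20% loss, and at rho=.7 both planned contrasts stay above .80 even with 30% lost by 9 months. This objection stands and limits the point to the calculation as printed. It does not remove the point, because the article states no correlation and does not use this argument to justify 159, and because loss lowers power in every row of both tables.

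A reader might also infer that the trial neglects retention. It does not: reminders, telephone completion, gift cards and FIML are all planned.

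Finally, this is a condensed article. Its power heading mentions a projected screen failure rate that the text never gives, so a retention figure may sit in the full protocol, and the mere absence of a rate is not the finding. The finding is that the recruited number equals the calculated number. No inflation can have been applied, whatever another document says.

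**Conclusion.** The point holds for the power statement as printed. The target of 159 carries no allowance for loss, and the 0.80 fails once two youths lack an outcome. On the article's own basis, power is about .78, .76, .70 and .64 at 5%, 10%, 20% and 30% loss; those rates are assumed.

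Whether the planned mixed model falls below 0.80 cannot be settled from the document. It depends on retention, on the within-person correlation and on which contrast is tested. At 10% lost by 3 months and 20% by 9 months, VR v Web ranges from .59 at rho=.4 to .87 at rho=.7, and GM v ST from .72 to .94. These values also assume compound symmetry and a .5 SD difference at 9 months.

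This is a correction that should be made to a figure readers will rely on. It is not a flaw in the design or the analysis model.

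**What to change.** Keep N=159, since logistics fix it. Restate the power paragraph at the number of youths expected to have 9-month CDI-2 data, in one of two ways:
- give the ANOVA-basis power at 10%, 20% and 30% loss (.76, .70 and .64); or
- give power for the two planned contrast-by-time tests over a stated range of retention and within-person correlation, for example .4 to .7.

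The second is better because it describes the analysis that will be run. In either case, do not say that 53 randomised per arm gives 0.80 power without naming the retention assumed.

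The cost is one recalculated sentence or a small table, with no added participants and no change to procedures. On the ANOVA basis the stated figure becomes less favourable.

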Notably, a recent systematic review of studies evaluating VR applications for mental health identified only 2 studies that have tested immersive VR mental health treatment approaches; both were uncontrolled feasibility trials targeting adults [19]. Thus, to our knowledge, this study will be the first randomized trial evaluating a brief VR intervention for adolescent depressive symptoms.

This research has 4 specific aims. Our first aim is to replicate past research suggesting that GM SSIs can significantly reduce depressive symptoms in at-risk adolescents. We hypothesize that adolescents aged 12 to 16 years who participate in a GMI (Web-based *or* VR–based) will show larger reductions in depression symptoms from baseline through the 9-month follow-up assessment compared with adolescents who receive an active, Web-based control program.

Our second aim is to evaluate new, single-session, VR GMI including a comparative efficacy study. Our second aim is to also evaluate whether the new VR–based GM SSI (the VR Personality Project) can reduce depressive symptoms in adolescents, both relative to an active control program and to the previously tested Web-based GM SSI [13,14]. We hypothesize that adolescents who participate in the VR–based GM SSI will show larger reductions in depressive symptoms from baseline through the 9-month follow-up assessment compared with adolescents who receive the Web-based GMI *and* compared with adolescents who receive the active Web-based control program.

Our third aim is to test whether shifts in perceived control mediate intervention effects on adolescent depressive symptoms. The VR Personality Project was designed to target and increase adolescents’ perceived control by offering a more immersive, active, and user-directed intervention experience than the Web-based GM SSI can provide. Thus, the third goal of this study is to examine whether the VR Personality Project does, in fact, reduce adolescent depressive symptoms by eliciting proximal increases in perceived control. We hypothesize that the VR Personality Project will lead to larger increases in immediate postintervention perceived control than the Web-based intervention from pre- to postintervention and that these increases will mediate subsequent reductions in adolescent depression across the follow up period.

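### The totals of 969, 159 and 66 belong to Cohen's f of .10, .25 and .40, not to d of .2, .5 and .8 across three arms; at a largest difference of d=.5, 159 gives omnibus power of about .62 to .75, not .80

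*Protocol article*

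**What the plan says.** The section on subjects, screen failure and power (Protocol article, Methods) describes a G*Power calculation for an omnibus F test on continuous depression symptoms, "with alpha=.05 and power at 0.80 for a 3-arm randomized trial". The effects are described as differences between group means, labelled small, medium and large. The result is: "Sample sizes calculated were 969, 159, and 66 for effects of .2, .5, and .8, respectively, for an omnibus one-way analysis of variance". The section concludes: "The sample size of 159 (53 per SSI condition) reflects power to detect a medium (*d*=.5) between-group effect size".

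Allocation is equal (Summary of Overall Study Design): "Participants will be randomly assigned to one of 3 conditions in equal numbers". The power section prints no value of Cohen's f, no conversion from d, and no assumed pattern for the three means.

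The Objectives do give an expected ordering. Both growth mindset arms should do better than supportive therapy, and adolescents in the VR arm "will show larger reductions in depressive symptoms from baseline through the 9-month follow-up assessment compared with adolescents who receive the Web-based GMI". The expected order is therefore VR, then Web-based growth mindset, then supportive therapy. No spacing is given.

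**The concern.** The effect size for a one-way ANOVA is Cohen's f, the standard deviation of the group means divided by the within-group standard deviation. The article states its effects as standardised mean differences. Turning d into f depends on the number of groups and on where the middle means lie. The familiar rule f = d/2 is a two-group result. If it lies behind a three-arm calculation, the sample size is too small for the difference it is said to detect.

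The statement about d=.5 is the article's only quantitative justification for N=159. If it is wrong, the trial is less sensitive than readers are told, and a non-significant result would be judged against a detectable effect that is too small. This is separate from attrition and from whether an omnibus ANOVA is the right basis for sizing a trial that will be analysed with mixed models.

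**Working it through.** **Inputs.** From the power section: k = 3 arms, alpha = .05, target power .80, omnibus one-way ANOVA, stated effects .2, .5 and .8, printed totals 969, 159 and 66. Equal arms of 53 come from the power and design sections. No dropout is applied, because the section states no allowance for it.

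**Formula.** Power = P(F′ > F_crit), where F_crit is the .95 quantile of F with 2 and N − 3 degrees of freedom, and F′ is noncentral F with the same degrees of freedom and noncentrality λ = N f². N rises in steps of 3 until power is at least .80.

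**Step 1: reproduce the printed figures.**

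| f entered | Smallest N | Power at that N | Printed |
|---|---|---|---|
| .10 | 969 | .801 | 969 |
| .25 | 159 | .805 | 159 |
| .40 | 66 | .818 | 66 |

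All three match exactly. Entering .2, .5 and .8 directly as f gives 246, 42 and 21, which do not match. The printed totals therefore belong to f = .10, .25 and .40, each being half of the stated d.

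**Step 2: convert d to f.** With equal groups and unit within-group SD, f is the SD (divisor k) of the group means.

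- Two groups, means (0, d): f = d/2.
- Three groups, means (0, d/2, d): f = d/√6 = .408d. This is the smallest f for a given largest difference.
- Three groups, means (0, 0, d) or (0, d, d): f = d√2/3 = .471d. This is the largest f.

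At d = .5, f runs from .408 × .5 = .204 to .471 × .5 = .236. No placement of the middle arm gives .25.

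**Step 3: power at N = 159 for d = .5.**

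- f = .25: λ = 159 × .0625 = 9.94, power .805.
- f = .236: λ = 159 × .0556 = 8.83, power .754.
- f = .204: λ = 159 × .0417 = 6.63, power .621.

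**Step 4: N for .80 power, with d as the largest difference.**

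| d | Printed N | N, one arm differs | N, middle arm halfway | Power at printed N |
|---|---|---|---|---|
| .2 | 969 | 1089 | 1449 | .617 to .750 |
| .5 | 159 | 177 | 237 | .621 to .754 |
| .8 | 66 | 72 | 96 | .636 to .768 |

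**Step 5: what 159 does detect.** Solving for exactly .80 power at N = 159 gives d = .527 (one arm differs) and d = .609 (middle arm halfway). Setting f = .25 exactly gives nearly the same: .25 × 3/√2 = .530 and .25 × √6 = .612.

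**Reference.** With complete data and d = .5, a two-sided t test has power .72 for one pair of arms (53 v 53) and .84 for the two growth mindset arms pooled against control (106 v 53).

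**The case against.** The strongest objection is that the article never says d=.5 is the largest of the three pairwise differences. Suppose instead it means pooled growth mindset against control, with VR modestly better than Web. Means of 0 (supportive therapy), .4 (Web) and .6 (VR) then give f = .249 and power .803. Means of 0, .5 and .6 give .84. If d=.5 is the gap between adjacent arms (0, .5, 1.0), power exceeds .99. This is correct arithmetic, and it shows that the result depends on what d refers to. But each of these patterns has a largest difference above .5 SD, and the power section states none of them. Read as one pair of arms differing by .5 SD, the claim also fails on a t test (.72).

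Second, .62 is the least favourable spacing, and the Objectives give an order without spacing. That stands: .62 is the bottom of a range. The top, .75, still falls short, though modestly.

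Third, .10, .25 and .40 are the conventional small, medium and large values of f, so the authors may have selected those benchmarks rather than halved d. That may be so. The totals would then be right for f and the fault would lie in the d labels. The mismatch between the printed N and the printed effect is the same.

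Fourth, efficacy will be tested by mixed-model contrasts over time, not by the omnibus F test, so the shortfall calculated here is not that of the planned tests. This is true, and the figures should not be read that way. The article nevertheless rests N on the omnibus test, and the stated power is not delivered for it.

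**Conclusion.** The concern holds. The printed totals are correct for f = .10, .25 and .40 and are mislabelled as d = .2, .5 and .8 in a three-arm design. Taking d=.5 as the largest between-arm difference, with equal arms, no dropout and alpha .05, omnibus power at N=159 is .62 to .75 depending on the middle arm. The type II error is therefore about 25% to 38% instead of the stated 20%. The difference detectable with .80 power is about d=.53 to .61. The result rests on that reading of d. Patterns that restore .80 need a larger maximum difference than the article states. The error is small in the most favourable pattern and material in the least favourable one.

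**What to change.** Keep N=159 and correct the statement in the power section:

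- Report 969, 159 and 66 as the totals for f = .10, .25 and .40.
- State that 159 gives .80 omnibus power, with complete data, for a largest between-arm difference of about d=.53 if one arm differs from two equal arms, and about d=.61 if the middle arm lies halfway.
- State that power at a largest difference of d=.5 is about .62 to .75.
- Remove the claim that 159 corresponds to d=.5.

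The cost is the rewording of two sentences and a slightly less favourable detectable effect. No participants are added and no analysis changes.

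### The stated sample sizes are those for Cohen's f of .10, .25 and .40 but are reported as effects of .2, .5 and .8, so N=159 does not give general 0.80 power for d=.5

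*Protocol article*

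**What the plan says.** The power section of the protocol article (Subjects, Projected Screen Failure Rate, and Power Analysis) says that G*Power was run for an omnibus F test on continuously measured depression symptoms, "with alpha=.05 and power at 0.80 for a 3-arm randomized trial". It reports: "Sample sizes calculated were 969, 159, and 66 for effects of .2, .5, and .8, respectively, for an omnibus one-way analysis of variance". It then concludes: "The sample size of 159 (53 per SSI condition) reflects power to detect a medium" between-group effect, given as d=.5. Cohen's f is not mentioned.

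Allocation is 1:1:1: "Participants will be randomly assigned to one of 3 conditions in equal numbers".

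The efficacy analysis in Aims 1 and 2 uses mixed-effects models. Aim 1 states: "We will create 2 orthogonal planned contrasts for testing intervention effects". One contrast sets both growth-mindset arms against supportive therapy (106 versus 53). The other sets VR against the Web-based growth-mindset arm (53 versus 53). Each is judged by its interaction with time. Aim 2 adds VR against supportive therapy, also 53 versus 53.

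**The concern.** The values .2, .5 and .8 are the usual small, medium and large conventions for Cohen's d, a difference between two means. G*Power's one-way ANOVA takes Cohen's f, whose conventions are .10, .25 and .40. Halving d to get f is right for two equal groups only. With three arms, an f of .25 requires a larger gap between the extreme arms than d=.5.

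This paragraph is the only power basis given for the efficacy comparisons on depression. If its label is wrong, a reader will credit the trial with a smaller detectable difference than the calculation supports. That matters most for the VR comparisons in Aim 2, which have 53 per arm.

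**Working it through.** **Inputs from the protocol:** three equal arms, alpha .05, target power 0.80, total N=159 (53 per arm), stated Ns 969/159/66.

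**Step 1. Reproduce the stated Ns.** For a one-way ANOVA with k=3, power = P(F′ > F crit), where F′ is noncentral F with k−1 and N−k degrees of freedom and λ = N·f². The smallest N in multiples of 3 with power of at least 0.80 is:

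| Effect read as | Small | Medium | Large |
|---|---|---|---|
| f = .10/.25/.40 | 969 (power .801) | 159 (.805) | 66 (.818) |
| f = .2/.5/.8, taken literally | 246 | 42 | 21 |
| Largest pairwise d = .2/.5/.8, two arms equal | 1089 | 177 | 72 |
| Largest pairwise d = .2/.5/.8, third arm midway | 1449 | 237 | 96 |

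Only the first row matches, and it matches all three figures exactly. The arithmetic is right for f; the label is wrong.

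**Step 2. Convert d=.5 to f for three equal arms.** f = √[Σ(μᵢ − μ̄)²/3], in SD units.
- Means 0, .25, .5: f = √[(.0625 + 0 + .0625)/3] = .204.
- Means 0, .5, .5: f = √[(.1111 + .0278 + .0278)/3] = .236. This is the largest f possible when the extremes differ by .5.

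So no arrangement with a largest d of .5 reaches f=.25. In reverse, f=.25 implies a largest d of .25/.4714 = .53 (two arms equal) to .25/.4082 = .61 (third arm midway).

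**Step 3. Omnibus power at N=159 when the largest d is .5.**
- Third arm midway: λ = 159 × .0417 = 6.6, power 0.62.
- Two arms equal: λ = 159 × .0556 = 8.8, power 0.75.
- For comparison, f=.25: λ = 159 × .0625 = 9.9, power 0.80.

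**Step 4. Two-group comparisons at d=.5.** Two-sided t test, noncentrality d·√[n₁n₂/(n₁+n₂)], full follow-up, no covariate adjustment.
- 53 versus 53: .5 × √26.5 = 2.57, power 0.72. Reaching 0.80 takes 64 per arm (192 in total).
- 106 versus 53: .5 × √35.33 = 2.97, power 0.84.

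**Step 5. Detectable d at 0.80 power, on the same basis.** The normal approximation is 2.80 × √(1/n₁ + 1/n₂).
- 53 versus 53: 2.80 × .194 = .54; exact t gives .549.
- 106 versus 53: 2.80 × .168 = .47; exact t gives .474.

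The protocol gives no loss rate. With an assumed 20% loss, the two detectable values become about .62 and .53.

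**The case against.** The case for leaving the paragraph alone has four parts.

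**The gap is small.** N=159 is a correct output for a conventional medium omnibus effect, and the pairwise detectable d is .55 rather than .5. For the Aim 1 contrast of pooled growth mindset against supportive therapy, d=.5 is covered at 0.84. The protocol also admits that small effects are out of reach. All of this stands. It limits the size of the error, but the effects attached to the three Ns are still wrong.

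**The planned analysis is not a simple comparison of means.** A reader might infer that the planned contrast-by-time tests also fall short of 0.80 at d=.5. The documents do not support that, because they give no within-person correlation. As an illustration, take equal correlation r between visits, no loss, no random slope and a normal approximation. The slope-difference statistic is then z = slope difference × √[53·S/(2(1−r))], with S the sum of squared time deviations (42 for months 0, 3, 9). For VR versus Web-based at r=.6:
- A d=.5 effect fully present by 3 months, time in months: z = (2/42) × √[53 × 42/0.8] = 2.51, power 0.71.
- A linear effect reaching d=.5 at 9 months: z = (.5/9) × √[53 × 42/0.8] = 2.93, power 0.83.
- The step effect with time coded by visit: power about 0.82.

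Over r of .4 to .7 and these shapes, power runs from about 0.54 to 0.92. No narrow range can be quoted. The unadjusted figures are likewise not power for the planned model.

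**Attrition.** A reader might count the absence of a dropout allowance as a further error. A condensed article can leave that to the full protocol, so it is not part of this point. The 20% figure is an assumption for illustration.

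**A one-sided test.** At one-sided .05, 53 versus 53 would have power 0.82. The protocol states no one-sided test, and its power basis is a non-directional F.

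**Conclusion.** The point holds, and its core needs no outside assumption: all three stated Ns match f of .10/.25/.40 exactly and match no reading of .2/.5/.8. The claim of power for d=.5 is therefore wrong as a general statement. It fails for the omnibus test on which it is based (0.62 to 0.75) and for simple pairwise comparisons (0.72). It happens to be true for the pooled comparison (0.84).

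The two-group figures assume a two-sided .05 test, complete follow-up and no adjustment for baseline or repeated measures.

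Two stronger readings should be resisted. The sample size itself is not shown to be wrong: 159 is right for f=.25, and the protocol attributes its size to logistical limits. Nor does the protocol say that a null VR result would be taken to exclude a medium effect. The risk is only that readers relying on the stated d could read it so.

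**What to change.** Keep N=159 and restate the power paragraph:
- Label the effects behind 969, 159 and 66 as Cohen's f of .10, .25 and .40, and say that 159 gives 0.80 power for an omnibus f of .25.
- Remove the general claim of power for d=.5 between groups.
- Add the d detectable with 0.80 power: about 0.55 for VR versus Web-based growth mindset and for VR versus supportive therapy, and about 0.47 for pooled growth mindset versus supportive therapy. Label these as unadjusted, two-sided, two-group figures with full follow-up, not as power for the contrast-by-time tests.
- If power for the planned mixed model or under loss to follow-up is wanted, state the correlation, effect shape, time coding and loss rate beside each figure. The detectable values of about 0.62 and 0.53 would carry the label of an assumed 20% loss.

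The cost is wording only, with no extra participants and no change to design or analysis. The stated detectable effect becomes slightly less favourable for the pairwise comparisons and slightly more favourable for the pooled one.
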